### Data analysis

The primary analysis will be by intention to treat; a per protocol analysis will be performed as a sensitivity analysis. Estimates of treatment effects with 95% confidence intervals ("targeted treatment" minus "best current care") will be calculated. Statistical tests (analysis of covariance (ANCOVA) for numerical outcomes; logistic regression for categorical outcomes) will be performed adjusted for imbalances in the baseline scores. Analyses will be carried out at each time point (4 and 12 months) for primary and secondary outcome measures; the primary endpoint is 12-month follow up. Analyses will be carried out to compare outcomes in patients randomised to "targeted treatment" or "best current care" separately for each of the three subgroups (high, medium and low risk) of patients classified according to the subgrouping tool.

An incremental approach will be used in the economic evaluation. The primary aim is to estimate and compare the societal costs associated with the study interventions and relate this to the difference in the number of quality-adjusted life years (QALYs). QALYs will be calculated by applying area-under-the-curve techniques to the EQ-5D scores at baseline, 4 months and 12 months.[53] Differences in costs and QALYs will be expressed using the incremental cost-per-QALY ratio, with uncertainty addressed using bootstrapping techniques, cost-effectiveness planes and acceptability curves.[54,55] The robustness of the results will be tested by conducting a number of sensitivity analyses; namely, the consideration of alternative perspectives (e.g. adopting an NHS perspective), the effect of incorporating 'generic' health care resource use and the application of multiple imputation techniques to deal with missing data.

An independent data monitoring committee will monitor the trial every 6 months. There will be no interim analyses.

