### Trial Objectives

The primary objective of this Trial is to compare the overall effectiveness of a "subgrouping for targeted treatment" approach with "best current care" (non-targeted) physiotherapy practice, over a 12 month period, for LBP. The targeted treatments are delivered by specially trained community physiotherapists.

Secondary objectives are: a) to investigate the change in prognostic indicators separately for each subgroup (high, medium and low risk) in the "targeted treatment" arm compared with the change in the corresponding subgroup in controls receiving "best current care" (non-targeted) physiotherapy practice; and b) To evaluate the cost effectiveness of the new model of care compared with "best current care".

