### Treatment allocation

Following completion of the baseline questionnaire, patients who consent to take part in the Trial are randomly allocated to one of the two treatment arms: "targeted treatment" or "best current care" (see Figure 1). After calculating the patient's STarT Back tool score from the postal questionnaire, the clinic administrator telephones the Primary Care Musculoskeletal Research Centre randomisation service.[15,34] Patients are randomised using a stratified block randomisation method according to Centre and risk subgroup. Random allocation is on a 2:1 (targeted treatment: best current care) ratio basis with a block size of three. This gives three possible permutations of treatment allocation per block: AAB; ABA; BAA. The research nurse in clinic is blinded to a patient's treatment allocation.

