### Sample size

The primary outcome measure for this trial is the Roland and Morris Disability Questionnaire (RMDQ) at 12-months. A difference of 2.5 points in RMDQ change scores is considered to be a minimum clinically important difference in the RMDQ.[52] Our sample size calculation is based on two separate hypothesis tests: (i) to test superiority of targeted treatment over best current care for high and medium risk subgroups; (ii) to test non-inferiority of the targeted treatment compared to best current care in the low risk subgroup. For the first hypothesis, a subgroup sample size of 160 patients (107 and 53 per arm based on a 2:1 allocation ratio) would enable detection of a between-group difference of 2.5 RMDQ points given 80–90% power, 5% (two-tailed) significance level, and a conservative standard deviation of 5 points. For the second hypothesis, the targeted treatment will be concluded as being non-inferior to best current care if the lower boundary of the 95% confidence interval for the difference in mean scores for targeted treatment minus best current care (among low-risk participants) is above the threshold of -2.5 points (equivalent to a one-sided test with significance level of 2.5%); 160 patients (107 and 53 per arm) allocated on a 2:1 basis would be able to demonstrate non-inferiority with 80–90% power. Pilot study data estimated that 25%, 50% and 25% of participants would be in the high, medium and low risk subgroups, respectively. These figures were used to extrapolate the total sample size requirement of 640 patients (160 in the high and low risk subgroups and 320 in the middle risk subgroup), which would ensure that we would have at least 80% power for carrying out all three subgroup analyses. 800 participants would need to be recruited to allow for a conservative 20% loss to follow up. Based on a 2:1 random allocation basis, we would therefore expect about 533 and 267 to be recruited to the "targeted treatment" and "best current care" arms, respectively.

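### The adjustment rule is tied to observed baseline imbalance and does not name the randomisation strata; a fixed covariate list would be clearer and at least as precise

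*Protocol article*

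**What the plan says.** The protocol article's Data analysis section names ANCOVA for numerical outcomes and logistic regression for categorical ones, and says that these "will be performed adjusted for imbalances in the baseline scores". It gives no criterion for an imbalance, and it does not say that the baseline value of the outcome is in every model. Neither Centre nor risk subgroup appears as a covariate, though nothing excludes them.

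The Treatment allocation section says: "Patients are randomised using a stratified block randomisation method according to Centre and risk subgroup". It adds: "Random allocation is on a 2:1 (targeted treatment: best current care) ratio basis with a block size of three".

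Two kinds of comparison follow. The primary objective under Trial Objectives is the overall contrast between the two arms over 12 months. The Data analysis section also compares the arms "separately for each of the three subgroups (high, medium and low risk) of patients classified according to the subgrouping tool". The Sample size section is built on these subgroup comparisons.

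**The concern.** An adjustment rule triggered by imbalance leaves the model open until the data are seen. Table 2 lists many measures with a baseline score. They are analysed at 4 and 12 months, and in three risk groups. The sentence does not let a reader say which model will be fitted for any of them. Where a prognostic baseline score happens to be balanced, the literal rule would leave it out and give up precision.

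The rule also works against the stratification. Blocking within Centre and risk subgroup makes those factors balanced, so an imbalance trigger would not bring them in. The tool that defines risk subgroup is described under Development of the Subgrouping Tool as resting on prognostic indicators, so the factor is meant to predict outcome. If it is balanced by design and then left out of the overall model, variation between risk groups stays in the error term. The reported standard error then exceeds the true sampling variation. The test is conservative: false positives are not inflated, but intervals are wider than they need be.

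**Working it through.** **Inputs from the protocol.** Difference 2.5 RMDQ points: "A difference of 2.5 points in RMDQ change scores is considered to be a minimum clinically important difference in the RMDQ". Standard deviation: "a conservative standard deviation of 5 points". Significance for superiority: "5% (two-tailed) significance level". Subgroup of 160 split 107:53; risk-group shares 25/50/25%; 640 evaluable and 800 recruited.

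**Step 1: reproduce the plan's figures.**
- SE in a 160-patient subgroup = 5 × √(1/107 + 1/53) = 0.840. Power = Φ(2.5/0.840 − 1.96) = 84.5%, inside the stated 80-90%.
- 160/0.25 = 640 and 640/0.8 = 800, as stated.
- Overall comparison, 640 patients at 2:1: SE = 5 × √(1.5 × 3/640) = 0.419. Power for 2.5 points is above 99.9%.

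**Step 2: baseline always in the model, risk subgroup omitted.** Let g be the gap in mean 12-month RMDQ between adjacent risk groups that remains after baseline adjustment. The protocol gives no value, so g is an assumption shown over a range. With shares 25/50/25 the between-group variance is 0.25g² + 0.25g² = 0.5g². The model SE becomes √(25 + 0.5g²) × √(1.5 × 3/640), while the true SE stays at 0.419 because the strata are balanced. The actual two-sided alpha is 2 × Φ(−1.96 × ratio).

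| g (points) | Model SE | Ratio to 0.419 | Actual alpha |
|---|---|---|---|
| 0 | 0.419 | 1.00 | 5.0% |
| 1 | 0.423 | 1.01 | 4.8% |
| 2 | 0.436 | 1.04 | 4.2% |
| 3 | 0.455 | 1.09 | 3.3% |
| 4 | 0.482 | 1.15 | 2.4% |

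**Step 3: simulation of the literal rule.** 1,500 trials per setting, 640 patients, blocks of three within two centres by three risk groups, ordinary least squares. Assumed inputs: baseline RMDQ means 5, 9 and 13 by risk group, within-group SD 4, slope on baseline 0.6, residual SD 5, no centre effect. In the conditional rule, baseline enters only if its between-arm difference has p < 0.05, and strata never enter. Each cell gives mean model SE / empirical SD / type I error.

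| Model | g = 0 | g = 1 | g = 2 |
|---|---|---|---|
| Baseline only if imbalanced | 0.484 / 0.453 / 3.0% | 0.506 / 0.460 / 3.2% | 0.531 / 0.459 / 2.5% |
| Baseline always, no strata | 0.419 / 0.418 / 5.3% | 0.423 / 0.419 / 5.1% | 0.431 / 0.419 / 4.3% |
| Baseline and strata always | 0.419 / 0.419 / 5.4% | 0.420 / 0.418 / 5.1% | 0.420 / 0.416 / 5.1% |

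The Monte Carlo error on a 5% rate is √(0.05 × 0.95/1500) ≈ 0.6 percentage points, so values from 5.1% to 5.4% do not differ from 5%. The trigger fired in only about 2% of trials, because stratifying by risk group already balances baseline RMDQ. The model SE under the conditional rule is therefore 0.484/0.419 = 1.16 to 0.531/0.420 = 1.26 times that of the full model. The true sampling variation is also larger: 0.453/0.419 = 1.08 to 0.459/0.416 = 1.10 times. In these settings most of the loss comes from making baseline conditional; leaving out the strata alone costs little.

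**The case against.** The strongest reply is that the sentence is a loose description of ordinary ANCOVA. It names ANCOVA without condition, ANCOVA needs a covariate, and no threshold or conditional word appears. On that reading the baseline score is always included and nothing depends on the data. This reading is plausible and cannot be ruled out. It does not settle the matter, because the sentence still ties adjustment to imbalance and the two readings give materially different models.

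A second reply is that a journal article may leave the covariate list to the full protocol or analysis plan, which are not shown. That stands: silence about the strata would not be a finding on its own. The point rests on the rule that is stated, under which strata balanced by design have no route into the model.

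A third reply is that risk subgroup is constant within each of the three subgroup analyses, on which the sample size rests, and that the overall comparison has ample power for 2.5 points. That also stands.

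Three stronger readings are tempting and not supported:
- A reader might infer that the plan adjusts for baseline scores and nothing else. The text does not say so.
- A reader might infer that omitting the strata alone makes the overall interval very much too wide. For the strata to explain 40% of the variance left after baseline, 0.5g²/(25 + 0.5g²) = 0.4 gives g ≈ 5.8 points between adjacent groups, more than twice the 2.5-point important difference. The protocol gives nothing to support such a gap.
- A reader might infer that fixed adjustment would raise subgroup power by a known amount. Ordinary ANCOVA may already deliver that gain, and the SD of 5 is already called conservative.

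**Conclusion.** The point holds in a limited form. The wording allows a data-dependent model and gives the stratification factors no place in it.

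- **If baseline enters only when imbalanced:** the overall model SE is about 0.48-0.53 against 0.42, with type I error about 2.5-3.2%. This rests on the assumed simulation inputs and a p < 0.05 trigger; another trigger would give other figures.
- **If baseline is always included:** omitting risk subgroup widens the overall SE by about 0-4% for residual gaps of 0-2 points and 9-15% for 3-4 points. The true gap is unknown.

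In both cases the error in the overall test is conservative. The stated 160, 640, 800 and 80-90% power are unaffected. Within the risk subgroups only the baseline rule (and Centre) is at issue, and that effect was not sized here. This is a worthwhile tightening of wording and does not threaten the trial's validity.

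**What to change.** Replace the phrase on imbalances with a fixed rule: every model adjusts for the baseline value of the outcome (where measured), Centre and, in the overall comparison, risk subgroup, always included regardless of observed imbalance. State that the logistic models use the same covariates. Outcomes without a baseline value, such as global change, keep the remaining terms. In the separate risk-group analyses the risk-subgroup term drops out because it is constant.

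The cost is one sentence. Baseline scores, Centre and risk subgroup are all known by the time of allocation, so no new data are needed and the sample size does not change.

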**High risk group**
• Assessing and addressing biopsychosocial risk factors by adopting cognitive behavioural principles to address unhelpful beliefs and behaviours.

**Table 2 T2:** Outcome Measures

	**Domain**	**Measures**	**Time Point (months)**
Primary	Pain and disability	Roland and Morris Disability Questionnaire [38]	0, 4, 12
	Catastrophising	Pain Catastrophising Scale [39]	0, 4, 12
Secondary	Back Pain	Pain intensity: 0–10 numerical rating scales of least & average pain in last 2 wks & current pain	0, 4, 12
		Duration – time since month back pain free [42]	0
	Back-related Leg symptoms	-Leg pain in last week	0, 4, 12
		-Location of leg pain	0, 4, 12
		-Description of pain	0, 4, 12
		-Presence of Numbness/parasthesia	0, 4, 12
	Pain elsewhere	Self complete manikin for bodily pain in last 4 weeks [43]	0, 12
	Global change	Compared to symptoms at baseline	4, 12
	Kinesiophobia	Tampa Scale Kinesiophobia [44]	0, 4, 12
	Illness perceptions	Musculoskeletal Illness Perceptions Questionnaire (MUSC-IPQ(R))^†^	0, 4, 12
	Anxiety/depression	Hospital Anxiety and Depression Scale [45]	0, 4, 12
	Health-related quality of life	Short Form 12 (version 2) [46]	0, 4, 12
	Patient satisfaction	-With current symptoms	0, 4
		-With information received	4
		-With care received	4
		-With back pain knowledge	4
		-Would have same treatment again	4
		-Rating of overall results of care	4
	Patient expectations	-Expectations for LBP status	0
		-Extent to which expectations were met	4
	Employment details	-Current employment status	0, 12
		-Satisfaction with employment	0, 12
		-Current/most recent job title	0, 12
		-Work loss due back problem	0, 12
		-Work loss due to other health problems	0, 4, 12
		-Work performance	0, 12
	Health care	-Primary care consultations	4, 12
	resource use	-Secondary care attendances (NHS and private)	4, 12
		-Additional health care practitioners (NHS and private)	12
		-Prescription and over-the-counter medicines and treatments	12
	Preference-based measure of health-related quality of life	EQ-5D [47]	0, 4, 12

^† ^Instrument in development, Personal Communication, [name].

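### Multiple imputation is kept for sensitivity analysis in the cost-utility analysis despite 20% planned loss, and the QALY difference is not tied to the planned baseline adjustment

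*Protocol article*

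**What the plan says.** The economic paragraph of the protocol article's Data analysis section constructs the outcome as follows: "QALYs will be calculated by applying area-under-the-curve techniques to the EQ-5D scores at baseline, 4 months and 12 months". It then states: "Differences in costs and QALYs will be expressed using the incremental cost-per-QALY ratio", with bootstrapping, cost-effectiveness planes and acceptability curves for uncertainty.

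Missing data appear once in that paragraph. The relevant sentence begins "The robustness of the results will be tested by conducting a number of sensitivity analyses" and goes on to name them: alternative perspectives, generic health care use, and "the application of multiple imputation techniques to deal with missing data". No method for missing data is given for the base case.

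The Sample size section inflates recruitment to 800 "to allow for a conservative 20% loss to follow up". The Outcome measures section assigns resource-use and work-absence data to the 12-month questionnaire. In Table 2, additional practitioners and medicines are collected at 12 months only.

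For the clinical outcomes, the preceding paragraph says that tests "will be performed adjusted for imbalances in the baseline scores" and that "Analyses will be carried out at each time point (4 and 12 months) for primary and secondary outcome measures". Table 2 lists EQ-5D in its secondary block, under "Preference-based measure of health-related quality of life", at 0, 4 and 12 months. The economic paragraph does not refer back to that adjustment.

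**The concern.** The role of imputation is a stated choice. A three-point area-under-the-curve QALY cannot be computed for a patient who lacks any of the three EQ-5D scores. A patient lost before 12 months lacks both the last score and some of the cost items. If nothing is imputed, such patients drop out of both parts of the ratio, including those who supplied baseline and 4-month EQ-5D. The result is then sound only if the remaining patients represent those lost within each arm. That is a stronger assumption than imputation needs when it uses the earlier scores. It also sits uneasily with the intention-to-treat principle set for the primary analysis.

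The second part is a matter of clarity. Baseline EQ-5D is a component of the QALY and also predicts the later scores. Unless the comparison is adjusted for it, a chance baseline difference passes into the incremental QALY, which is the denominator of the ratio. Cost-effectiveness is one of the trial's named secondary objectives.

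**Working it through.** **Inputs from the protocol article.** EQ-5D at 0, 4 and 12 months; 800 recruited, 2:1, about 533 and 267; 640 required after 20% loss; stratification by Centre and risk subgroup.

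**Inputs assumed, because the article gives none.** EQ-5D SD 0.25-0.30; slope *b* of follow-up on baseline EQ-5D 0.3-0.7; the pattern of missing visits.

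1. *The plan's own figure.* 160/0.25 = 640, and 640/(1 - 0.20) = 800. The stated total reproduces. The article gives no numerical figure for the economic analysis.

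2. *Patients with a computable QALY.* If the 20% planned for the 12-month RMDQ also applies to EQ-5D, 800 × 0.80 = 640 patients have a 12-month score. This is the most that a base case without imputation could use at that loss. If 20% are also missing at 4 months (a further assumption), the number is 640 when the same people are missing, 800 × 0.64 = 512 when losses are independent, and 800 × 0.60 = 480 when they do not overlap. Gaps in cost items would lower these further.

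3. *Weights in the QALY (trapezoid rule, in years).*
   - Baseline: (4/12)/2 = 1/6
   - 4 months: (4/12)/2 + (8/12)/2 = 1/2
   - 12 months: (8/12)/2 = 1/3

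   A patient lost after the 4-month visit has already supplied scores carrying 1/6 + 1/2 = 2/3 of the weight. A complete-case base case uses none of it.

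4. *Effect of a baseline difference d without adjustment.* Shift in QALY difference = d × (1/6 + b × 5/6).
   - b = 0.3: multiplier 1/6 + 0.25 = 0.417
   - b = 0.7: multiplier 1/6 + 0.583 = 0.75

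5. *How large d is by chance.* SE = SD × √(1/533 + 1/267) = SD × 0.075, so 0.019 at SD 0.25 and 0.022 at SD 0.30. A difference of 0.02 is therefore about one standard error. Stratification by risk subgroup is ignored here and should reduce it.

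6. *Result for d = 0.02.* 0.02 × 0.417 = 0.008 and 0.02 × 0.75 = 0.015 QALY. Regressing the QALY on baseline EQ-5D would remove this term.

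**The case against.** The strongest reply is that most of this is silence in a condensed article. The QALY sentence describes how each patient's QALY is built, not how the arms are compared, and that construction is fully compatible with later regression on baseline EQ-5D. The same section commits to baseline adjustment for primary and secondary outcomes, and EQ-5D is among the latter. Imputation is pre-specified, so readers would see whether the result depends on missing data.

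Much of this stands, and it rules out several stronger readings that a reader might infer:

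- *That the plan fixes an unadjusted QALY comparison.* The article never says so. It only fails to connect the economic analysis with the adjustment it plans elsewhere.
- *That a complete-case base case is laid down.* It is the likeliest reading, but no method is named.
- *That baseline imbalance biases the result.* Under randomisation a chance imbalance adds imprecision. The bootstrap reflects that variability, although it does not remove the shift in the trial actually run.
- *That imbalance will probably decide the sign of the QALY difference.* The article gives no expected QALY difference against which to judge this. An imbalance of 0.05 would move it by 0.05 × 0.417 = 0.021 to 0.05 × 0.75 = 0.038, but 0.05 is 2.2 to 2.7 standard errors under the same SDs, a two-sided chance of roughly 1-3%.
- *That only 64% of patients would contribute.* This needs independent 20% loss at both visits. The article calls its 20% conservative and uses it for the 12-month RMDQ.

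The reply does not reach the placing of multiple imputation. The article names it as a sensitivity analysis, so that is not an omission left to a fuller document. Nor is it only a matter of ordering, because the base case is the headline result.

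**Conclusion.** The point holds in a limited form. The article keeps multiple imputation out of the base-case cost-utility analysis while planning for 20% loss. If the base case is complete-case, at that loss it would use at most about 640 of 800 patients and would set aside the observed 4-month scores of those lost later. This part rests on the article's own text and figures, except that complete-case handling is inferred and the 20% is carried over from the RMDQ calculation.

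The baseline-adjustment part is a request to state the method. A one-standard-error imbalance would be worth about 0.008-0.015 QALY, conditional on the assumed SD and slope, and adjustment would remove that imprecision at almost no cost. The matter concerns a secondary objective and does not touch the RMDQ analysis or the sample size, which reproduces.

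**What to change.** In the economic part of the Data analysis section:

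- Make multiple imputation the base case for missing EQ-5D and cost data. Impute separately by arm, use the baseline and 4-month data, and say how imputation is combined with the bootstrap.
- Estimate incremental QALYs by regression on baseline EQ-5D, Centre and risk subgroup.
- Report complete-case and unadjusted results as sensitivity analyses.

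This needs a change of wording and modest extra programming. No new data are required, since imputation is already planned and baseline EQ-5D is already collected. The downside is that the base case then relies on a missing-at-random imputation model; the complete-case sensitivity analysis would show how far the result moves without it.
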